### Interim analyses {21b}

There will be weekly meetings between the research nurses and the investigators throughout the study period. The meetings will evaluate the progression of the trial and adverse events.

### Methods for additional analyses (e.g., subgroup analyses) {20b}

We will also conduct per-protocol analyses, including those restricted to intervention participants actively taking part in the intervention for at least 8 of the 16 weeks (50%). This will be conducted for both primary and secondary outcomes. We will also conduct sub-group analyses for participants with less or more than the median number of steps in the 4-min step test.

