### Outcomes measures {12}

The data collection will take place within the patient’s local OAT clinic and the research nurse will lead the collection. The nurse has training in performing these tests, both as part of the annual assessment and in the pilot study.

Primary outcome measure:

Psychological distressThe primary outcome is psychological distress 12–16 weeks after intervention initiation assessed with the Norwegian-validated translation of the ten-item version of the Hopkins Symptom Checklist (SCL-10) [27]. SCL-10 is a valid, reliable, relatively brief, and easy tool to implement for assessing psychological distress symptoms. SCL-10 will be evaluated with mean SCL-10 item score, and compared between the intervention and control arm.

Secondary outcome measures 12 to 16 weeks after intervention initiation:Physical functioning assessed with a 4-min step test measuring the number of steps climbed in the period [28].Physical activity assessed using the Norwegian-validated translation of the International Physical Activity Questionnaire (IPAQ) [29].Changes in fatigue will be assessed with the Fatigue Symptom Scale (FSS-3) [30].Changes in health-related quality of life assessed with EuroQoL EQ-5D-5L [31, 32] in addition to a self-reported question on happiness on a 0 to 10 scale.Changes in self-reported substance use will be assessed comparing change in overall substance use (using a semi-continuous substance use score from 0 to 1 including frequency of intake of several substances) by before intervention and in a 1-year follow-up visit [11].Adherence to OAT (as proportion in each arm who 1 year after initiation of the intervention is receiving OAT with active follow-up during last month).Biochemical indicators of inflammation (measured with C-reactive protein in serum and total leukocyte count in blood).◦ Sub-group (*n* = 60): IFN-gamma, IL-1beta, IL-1RA, IL-6, IL-8, IL-10, IL-17A, MCP-1, TNF-alfa measured in dried blood spots.

Baseline characteristics as predictors for degree of active participation in the physical activity interventions will be assessed.

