### Sample size {14}

Based on a cohort study in the same population [11], we assume that psychological distress assessed with a mean item score of SCL-10 score is 2.2 with a standard deviation of 0.8. To detect a reduction in psychological distress to a mean level of SCL-10 of 1.8 which is under the typically used threshold of 1.85 for substantial psychological distress [27], among participants taking active part in intervention and being evaluated among those randomized to intervention groups, with 62.5% of the participants randomized to the intervention assumed to take active part in intervention (i.e., a mean among those randomized to the intervention of 1.95), with 80% power a 1.1 intervention: control ratio, a two-sided test, and alpha (*α)* error of 5%. Based on these assumptions, 324 persons are required in total, including 162 persons in the intervention arm and 162 persons in the control arm (statistical power was calculated in Stata SE 17.0).

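### The per-protocol analysis selects attenders in the exercise arm only, so it is not a randomised comparison; a complier-average estimate should be added as the main estimate of the effect of participation

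*Protocol article*

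**What the plan says.** The section Methods for additional analyses {20b} of the protocol article plans per-protocol analyses, among them analyses "restricted to intervention participants actively taking part in the intervention for at least 8 of the 16 weeks (50"%). They cover primary and secondary outcomes. The section sets no restriction on controls and does not name the control group to be used.

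Other sections bear on this:

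- Explanation for choice of comparators {6b}: controls receive standard treatment and are not offered the exercise programme.
- Criteria for discontinuing {11b}: participants may leave the programme whenever they wish.
- Outcomes measures {12}: "Baseline characteristics as predictors for degree of active participation in the physical activity interventions will be assessed".
- Statistical methods {20a}: the main analyses follow intention-to-treat. Baseline confounders may be adjusted for if they are imbalanced, and a detailed analysis plan is to follow.
- Sample size {14}: the control mean and spread are a "mean item score of SCL-10 score is 2.2 with a standard deviation of 0.8". The calculation starts from 1.8 among active participants, "with 62.5% of the participants randomized to the intervention assumed to take active part in intervention", which gives "a mean among those randomized to the intervention of 1.95".

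**The concern.** The 8-week rule is applied to behaviour after randomisation, in one arm only. Exercise participants who do not attend are dropped, while the controls who would not have attended stay in. If attenders differ from non-attenders in the distress they would have had anyway, the contrast mixes that difference with the effect of exercise. The data cannot show how much of the result is due to selection, because would-be attenders cannot be identified among the controls.

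At stake is the trial's estimate of what exercise does for those who take part. With 37.5% expected not to be active, that is a natural question for clinics deciding whether to adopt the programme, and the planned comparison is not a sound way to answer it.

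**Working it through.** **The plan's own figure.** All inputs are from Sample size {14}: 2.2 in controls, 1.8 in active participants, SD 0.8, 62.5% active, 80% power, two-sided 5%. The allocation ratio is printed as 1.1, but the equal arms and the Trial design section show that 1:1 is meant.

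- Diluted mean: 0.625 × 1.8 + 0.375 × 2.2 = 1.95.
- Difference used: 2.2 − 1.95 = 0.25.
- A two-sample t-test needs 161.7 per arm, so 162 per arm and 324 in total. The stated figure is reproduced exactly.

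**Bias of attenders against all controls.** Let A and N be the untreated mean SCL-10 of would-be attenders and would-be non-attenders, and let g = N − A. By randomisation the control arm has mean 0.625A + 0.375N. With no exercise effect the attenders have mean A. The contrast is therefore 0.625A + 0.375N − A = 0.375 × g.

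**Precision.** If the 62.5% also meet the 8-week rule, there are 0.625 × 162 ≈ 101 attenders against 162 controls. SE = 0.8 × √(1/101 + 1/162) = 0.101.

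**Results.** The protocol gives no value for g, so it is varied. The rejection column assumes no true effect and no covariate adjustment. The last column assumes a true effect of 0.40 in attenders.

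| Assumed g | Bias | Rejection with no effect | Per-protocol estimate if true effect is 0.40 |
|---|---|---|---|
| −0.4 | −0.15 | about 32%, against exercise | 0.25 |
| 0 | 0 | 5% | 0.40 |
| 0.2 | 0.075 | about 12% | 0.475 |
| 0.3 | 0.11 | about 20% | 0.51 |
| 0.4 | 0.15 | about 32% | 0.55 |

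A simulation of 10,000 trials at g = 0.4 with no effect agrees: mean per-protocol difference 0.15, with 32% rejections. Intention-to-treat rejected in 5%, and the complier-average estimate averaged about 0.

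**The alternative.** The complier-average effect is the intention-to-treat difference divided by the participation share: 0.25/0.625 = 0.40, which is the 2.2 to 1.8 drop assumed among active participants.

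- Intention-to-treat SE: 0.8 × √(2/162) = 0.0889.
- Complier-average SE: approximately 0.0889/0.625 = 0.142.
- 95% interval: 0.40 ± 1.96 × 0.142, or 0.12 to 0.68.
- Ratio of estimate to SE: 0.40/0.142 = 2.81, the same as 0.25/0.0889. Power and sample size do not change.

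**Its weak point.** With the 8-week cut-off as exposure, the method assumes no effect in those attending 1 to 7 weeks. If everyone below the cut-off gains 0.1, the intention-to-treat difference becomes 0.625 × 0.40 + 0.375 × 0.1 = 0.2875, and the estimate 0.2875/0.625 = 0.46. A gain of 0.2 gives 0.325/0.625 = 0.52.

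**The case against.** The strongest reply is that this is an additional analysis, that intention-to-treat is fixed for the main analyses, and that the comparator, adjustment and labelling can be settled in the analysis plan still to come. The first two parts stand: the primary conclusion is untouched. The third stands only in part, because {20b} already fixes the restricted arm, the cut-off and the outcomes.

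Several stronger readings are tempting, but the document does not support them:

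- A reader might infer that a complier-average analysis answers the question for which the trial was sized. It does not. The 324 rests on the diluted difference of 0.25, which the main analysis addresses; 0.40 is an assumption upstream of it.
- A reader might infer that the attenders-only result will become the trial's headline. Nothing in the protocol says so.
- A reader might infer that the bias must favour exercise. The sign of g is unknown. The Discussion names better health as a leading motive to exercise, so more distressed patients could attend more.
- A reader might infer that the protocol expects attendance to depend on baseline characteristics. It says only that such predictors will be assessed.
- Comparison with all controls is the natural reading, but it is not written.

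The rejection rates are also for an unadjusted contrast. SCL-10 is measured at screening, and whatever part of g it carries could be adjusted away. The complier-average estimate has its own assumption, and breaking it can inflate the result by as much as the selection bias shown here. It rescales the intention-to-treat result and is not new evidence of efficacy. That argues for adding it with its assumptions in view, not for treating it as a correction free of assumptions.

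Finally, the outcome is taken at 12–16 weeks while attendance counts over 16, so someone assessed at week 12 could qualify on later attendance. This can affect only those with 4 to 7 active weeks by then, and it cannot be sized from the document.

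**Conclusion.** The point holds as a limited one. The planned per-protocol contrast is not protected by randomisation, and its bias is 0.375 × g for a gap g that the protocol does not give. Over assumed gaps of 0 to 0.4 the bias runs from 0 to 0.15 points, and unadjusted rejection with no effect from 5% to about 32%. A negative gap reverses the direction.

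These figures assume that the whole control arm is the comparator and that 62.5% meet the 8-week rule. The protocol does not define active part in Sample size {14}, so it is not shown to mean the same as that rule.

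**What to change.** - Add a complier-average estimate as the main estimate of the effect of participation, using two-stage least squares with randomised arm as instrument. Keep all randomised participants and adjust for baseline SCL-10 and site.
- Make any-session participation the main exposure, or give it and number of sessions at least equal weight with the 8-week cut-off.
- State the assumptions. The any-session version assumes that the offer alone does nothing for those who never attend, and it cannot test this. The 8-week version also assumes no effect in those attending 1 to 7 weeks.
- Keep the attenders-only comparison only as exploratory and non-randomised. Name its control group and adjust it for baseline SCL-10 and predictors of attendance.

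The cost is a little more analysis work and a wider interval (SE about 0.142, against 0.101 for the attenders-only contrast). No further participants or visits are needed. Table 1 lists no attendance record, but the 8-week rule and the planned study of participation already require one. The change can be made in the detailed analysis plan that Statistical methods {20a} promises before data export.

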### Trial design {8}

A multicentre individually randomized controlled trial, parallel groups, 1:1 allocation ratio, superiority trial.

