### Participant timeline {13}

See Table 1: Flow chart of the study outlining follow-up visits and assessment at each visit.

**Table 1 Tab1:** Flow chart of the study outlining follow-up visits and assessments at each visit

	**Screening (research nurse)**	**Treatment follow-up week 0 to 16 (nurses/social workers)**	**Intervention end-assessment (12–16 weeks after initiation)**	**Intervention post-assessment (10–30 weeks after intervention) initiation)**	**Annual follow-up**
**Research nurse assessment**	X		X	X	X
- Informed consent	X				
- Eligibility assessment	X				
- Follow-up by OAT staff		X			
- Clinical assessment	X		X	X	X
Biochemical tests	X		X	X	X
Physical funct. (4-min step test)	X		X	X	X
Physical activity. (IPAQ)	X		X	X	X
Psychological distress (SCL-10)	X		X	X	X
Fatigue symptoms (FSS-3)	X		X	X	X
Quality of life EQ-5D-5L	X		X		X

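### The only planned subgroup analysis splits the 4-min step count at its median, with no time point given, and cannot show whether the effect differs by fitness; a screening-count-by-arm interaction would do so at almost no cost

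*Protocol article*

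**What the plan says.** The section on additional analyses {20b} names one subgroup analysis of the treatment effect: "We will also conduct sub-group analyses for participants with less or more than the median number of steps in the 4-min step test". (The subgroup of 60 in the outcomes section is a laboratory subset for cytokines, not a treatment-effect subgroup.)

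The splitting variable is also a secondary outcome in Outcomes measures {12}: "Physical functioning assessed with a 4-min step test measuring the number of steps climbed in the period". In Table 1, under Participant timeline {13}, the row "Physical funct. (4-min step test)" is marked at screening, at the end-assessment, at the post-assessment and at the annual follow-up. A pre-randomisation value therefore exists, but {20b} does not refer to it.

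No treatment-by-subgroup interaction is mentioned anywhere in the article. The statistical methods section {20a} sets significance at p < 0.05, promises estimates with 95% confidence intervals, and leaves detail to an analysis plan to be written before data export.

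**The concern.** A subgroup analysis by fitness should tell us whether fitter and less fit patients respond differently to exercise. The sentence in {20b} chooses the variable, the cut-point and a format of one analysis per half. Three weaknesses follow.

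- The measurement occasion is open, and the test is one that exercise is meant to improve.
- Steps are whole numbers, so ties at the median are plausible, and those participants belong to neither half.
- Two separate half-sample results do not estimate the difference between the halves. A significant result in one half and a non-significant one in the other invites the reading that only one kind of patient benefits, when chance alone often produces that pattern.

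At stake is a misleading secondary message about whom the programme helps, together with information lost by cutting a count that is collected in full.

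**Working it through.** **Inputs, all from the article.** The sample size section {14} gives a control level as "mean item score of SCL-10 score is 2.2 with a standard deviation of 0.8" and, for the intervention arm, "a mean among those randomized to the intervention of 1.95". It assumes 80% power and a two-sided 5% test, with 162 persons per arm. That section prints the ratio as 1.1, but the equal arms and the Trial design section ("parallel groups, 1:1 allocation ratio, superiority trial") show that 1:1 is meant.

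**Reproducing the plan's own figure.**
- Diluted mean with 62.5% taking part: 0.625 × 1.8 + 0.375 × 2.2 = 1.125 + 0.825 = 1.95. The difference is 2.2 − 1.95 = 0.25, and the standardised effect is 0.25 / 0.8 = 0.3125.
- Normal approximation: n per arm = 2 × (1.960 + 0.842)² × 0.8² / 0.25² ≈ 161, or 322 in total. The t-based calculation gives 162 per arm (power 80.07%), or 324 in total. The stated sample size reproduces.

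**Power in each half, using a screening split.** A median split leaves about 324 / 2 = 162 participants per half, or about 81 per arm if the arms are balanced within halves and few participants are tied.
- Standard error of the difference: 0.8 × √(2/81) = 0.1257.
- 0.25 / 0.1257 = 1.989, and Φ(1.989 − 1.960) ≈ 0.51. The t-based value is 50.7%.

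**Chance disagreement under a uniform effect.** Let the true effect be 0.25 in both halves and treat the halves as independent. With p = 0.511, the probability that exactly one half is significant is 2 × p × (1 − p) = 2 × 0.511 × 0.489 ≈ 0.50. A simulation of 6,000 trials agreed: exactly one half significant in 50.1%, both in 24.8%, neither in 25.1%.

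**What a direct comparison of the halves could detect.** The standard error of the difference between the two half-specific effects is 0.8 × √(4/81) = 0.178.
- Power for a between-half difference of 0.25: Φ(0.25/0.178 − 1.960) ≈ 29%.
- Difference detectable with 80% power: (1.960 + 0.842) × 0.178 ≈ 0.50, twice the planned main effect.

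**Information lost by the cut.** For a roughly normal covariate, the squared correlation between the covariate and its median-split indicator is 2/π ≈ 0.64. For a linear interaction this is roughly equivalent to using 0.64 × 324 ≈ 207 participants instead of 324.

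**Which time point matters.** In 4,000 simulated trials per setting with no effect of exercise on SCL-10, a split at the pooled follow-up median gave false differences of about +0.05 to +0.13 points (against exercise) in each half. This assumed that exercise raises steps by 0.3 to 0.5 SD and that steps correlate −0.3 to −0.5 with SCL-10. Neither assumption comes from the article. With a screening split, simulated at 0.5 SD and −0.3, the bias was about 0 and rejection was 4% to 5% per half.

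**The case against.** The strongest reply is that most of this is detail that a condensed article may leave to its analysis plan, and {20a} announces such a plan. That stands for the time point, the tie rule and the interaction test taken singly: none of these omissions would be a finding on its own. The sentence also does not forbid an interaction term, nor does it say that separate p-values will be compared. The 50% figure therefore measures the risk of a reading that the format invites, not an inference that the authors announce; it applies to any trial of about 80% power cut in half. A median split is inefficient, not invalid, and the analysis is listed as additional.

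A reader might go further and infer that the subgroups will be formed on a follow-up step count and so are biased. The documents do not support that. No passage says a follow-up value will be used, Table 1 provides a screening value, and the size of any bias rests wholly on assumed shifts and correlations. Nor is it a fault that the step test is also an outcome: a split on its screening value is not biased for that reason.

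What the reply does not remove is that {20b} already commits to a cut-point and a within-half format. An analysis plan that followed it literally would inherit a method that answers the question less well than one using data already collected.

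**Conclusion.** The point holds as a cheap improvement of low priority. As written, the subgroup rule leaves the measurement occasion and ties at the median unsettled. Even on its most favourable reading, it offers two analyses with about 51% power each, which would disagree on significance in about half of trials if the effect were uniform. These figures rest on the protocol's own difference and SD, complete data and an even split. The 64% figure assumes a roughly normal step count and a linear interaction.

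Post-randomisation bias is a conditional risk, not something the plan commits to. The intention-to-treat primary analysis and the sample size are untouched.

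**What to change.** Replace the subgroup sentence in {20b}, or specify it in the analysis plan before data export, along these lines:

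*Effect modification by physical functioning will be explored by adding the screening 4-min step count, as a continuous variable, and its interaction with trial arm to the primary model. The interaction estimate will be reported with its 95% confidence interval. The analysis is exploratory.*

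If a median split is also shown, base it on the screening count, assign participants at the median to a named group, and draw no conclusion from the separate p-values.

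The cost is one sentence and no new data. The small downside is that linearity of the interaction must be assumed or checked. The trial was not sized for an interaction, so the result should be read from its confidence interval.

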### Methods in analysis to handle protocol non-adherence and any statistical methods to handle missing data {20c}

If any variables are missing of the primary outcome, they will be handled using an intention-to-treat strategy; the baseline value will be used.

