### Plans to promote participant retention and complete follow-up {18b}

We assume participants will form a positive group dynamic which will promote participant retention. Further, we assume the intervention will be experienced as useful, which will also contribute to participant retention. Participants will also receive weekly appointment reminders and follow-ups from the research and clinical staff.

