## Statistical methods

### Statistical methods for primary and secondary outcomes {20a}

A detailed plan/protocol for analysis will be developed before data export and analysis adhering to the SPIRIT guidelines. Analysis methods and presentation of results will follow the CONSORT guidelines [33–35]. All tests will be two-sided. Descriptive results and efficacy estimates will be presented with 95% confidence intervals, and the statistical significance is set at *p* < 0.05. Potential confounders may be considered for adjustment if they are imbalanced at baseline, with assumed meaningful differences. Missing data will be considered, and appropriate imputations based on pre-defined assumptions will be done when necessary, as described in a detailed analysis plan. Categorical variables will be summarized as percentages and continuous variables as medians with interquartile ranges or means with standard deviation for variables with a Gaussian distribution. The primary outcomes will be analyzed with generalized linear models, Gaussian distribution. The main analyses will be analyzed as intention-to-treat.

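### Replacing each missing primary SCL-10 value with the baseline value shrinks a real effect and can bias the comparison when missingness differs by arm

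*Protocol article*

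**What the plan says.** Section {20c} gives one rule for a missing primary outcome: "they will be handled using an intention-to-treat strategy; the baseline value will be used". Section {20a} is more open and says that "appropriate imputations based on pre-defined assumptions will be done when necessary, as described in a detailed analysis plan". It names a Gaussian generalised linear model for the primary outcome, without saying whether baseline SCL-10 is a covariate.

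Section {14} takes a "mean item score of SCL-10 score is 2.2 with a standard deviation of 0.8". The target is stated as "To detect a reduction in psychological distress to a mean level of SCL-10 of 1.8", and it applies "among participants taking active part in intervention and being evaluated among those randomized to intervention groups". The active share of the exercise arm is put at 62.5%, and the intervention-arm mean is therefore set at 1.95. The result is that "324 persons are required in total, including 162 persons in the intervention arm and 162 persons in the control arm". No allowance for missing outcomes is mentioned.

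On retention, section {18b} begins: "We assume participants will form a positive group dynamic which will promote participant retention". It then adds an expectation that the intervention will be found useful, and weekly reminders and staff follow-up.

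**The concern.** Carrying the baseline forward assigns zero change to every participant without a follow-up value. This is a strong assumption about unseen outcomes, and calling it intention-to-treat does not support it.

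Two things are at stake for the primary endpoint. A real effect is pulled towards zero in a trial whose sample size has no margin for it. And if SCL-10 drifts in both arms, for example through ongoing care or because people enter at a bad time, the arm with more missing values is credited with less of that drift. The difference then enters the estimate as if it were a treatment effect. The second problem can favour either arm, so the rule cannot be defended as simply conservative.

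**Working it through.** **Inputs from section {14}:** control mean 2.2, SD 0.8, mean 1.8 among active participants, 62.5% active, 162 per arm, two-sided 5%. **Assumed, not in the documents:** missing proportions m_I (exercise) and m_C (control), an improvement c shared by both arms, and a baseline–follow-up correlation of 0.6.

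**1. The plan's own figure.** The diluted mean is 0.625 × 1.8 + 0.375 × 2.2 = 1.95, a difference of 0.25. A two-sample t-test with SD 0.8 needs 161.7, so 162 per arm and 324 in total, as stated. Power with all 324 outcomes observed is 80.1% (80.3% by the normal approximation used below). There is no slack.

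**2. What the rule estimates.** Write e for the true benefit (reduction in SCL-10). If missingness is unrelated to outcome and participation, the mean improvement is (1 − m_I)(e + c) in the exercise arm and (1 − m_C)c in control. The estimated benefit is therefore

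(1 − m_I) × e + (m_C − m_I) × c.

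**3. Equal missingness, no baseline adjustment.** The second term vanishes. With substitution, 162 per arm enter the analysis and SE = 0.8 × √(2/162) = 0.0889. On observed cases the difference stays 0.25, but n per arm falls to 162(1 − m).

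| m | Substitution: difference | Power | Observed cases: n per arm | SE | Power |
|---|---|---|---|---|---|
| 20% | 0.80 × 0.25 = 0.20 | 61% | 129.6 | 0.0994 | 71% |
| 30% | 0.70 × 0.25 = 0.175 | 50% | 113.4 | 0.1062 | 65% |

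The fall from 80% to 71% or 65% is the cost of having no loss allowance. The further fall to 61% or 50% is the cost of the rule.

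**4. Equal missingness, baseline-adjusted (correlation 0.6).** Substitution raises the correlation with baseline to m + (1 − m) × 0.6.
- At 20% the correlation is 0.68. The residual variance is 0.64 × (1 − 0.68²) = 0.344, plus 0.005 for mixing treated and carried-forward values, and SE = 0.0656. Power for 0.20 is 86%. Observed cases: residual SD 0.8 × √(1 − 0.36) = 0.64, SE 0.0795, power for 0.25 is 88%.
- At 30% the correlation is 0.72 and SE = 0.0623. Power for 0.175 is 80%, against 84% on observed cases.

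Adjustment restores most of the power, but the estimate is still 0.20 or 0.175.

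**5. Unequal missingness with a shared change.**
- m_I = 30%, m_C = 15%, c = 0.2, e = 0.25: 0.70 × 0.25 − 0.15 × 0.2 = 0.175 − 0.030 = 0.145.
- m_I = 15%, m_C = 30%, c = 0.3, e = 0: 0.15 × 0.3 = 0.045 in favour of exercise. Unadjusted, 0.045/0.0889 = 0.51 standard errors, giving a two-sided type I error of about 8%. Adjusted, the SE is about 0.0658, the shift is 0.68 standard errors, and the error rate is about 11%.

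Simulation agrees with these results. In both cases the observed-data analyses recover the true value, with type I error near 5% in the second.

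**6. When dilution does no harm.** Suppose every missing exercise-arm outcome falls among the 37.5% already given no effect, and c = 0. Substitution then gives 0.625 × 1.8 + 0.375 × 2.2 = 1.95 again, so the 0.25 and the 80% survive.

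**The case against.** Several objections have force.

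- **The dilution may be planned.** Section {14} applies the 1.8 to participants who are both active and evaluated, and gives the other 37.5% no effect. If those who stop exercising are those who miss the assessment, substitution reproduces the planned 0.25. In that situation observed cases that ignore attendance would overstate the effect: at 20% missing, 0.40 × 0.625/0.80 = 0.3125. This stands as a condition on the shrinkage. But the text does not say that missing outcomes are confined to that group, and any among the active 62.5% lower the estimate.
- **The power loss can be overstated.** A reader might set 61% (substitution, unadjusted) beside 88% (observed data, adjusted) and blame the rule for the whole gap. Most of it is baseline adjustment, on which section {20a} is silent. Like for like, the rule costs about 10 to 15 points unadjusted and 2 to 4 points adjusted.
- **The standard error is not at fault.** A reader might infer that imputed values give false precision. Each substituted value is the participant's own measurement, and in simulation at 20% missing the model SE matches the empirical spread (0.089 against 0.090 unadjusted, 0.066 against 0.065 adjusted). The excess type I error comes only from the shifted estimate.
- **Unequal missingness is not shown.** The group dynamic and perceived usefulness in section {18b} concern the exercise arm, so a reader might take imbalance as expected. But the same section lists reminders and follow-up without restriction by arm, and both arms are assessed in the same clinics. Without a shared change, moreover, imbalance produces no false effect.
- **Sections {20a} and {20c} need not conflict.** The first defers to an analysis plan that is not shown, which may contain sensitivity analyses. None can be called absent.

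What remains is that the one rule the article fixes for the primary endpoint is unsound in ordinary circumstances.

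**Conclusion.** The point holds, within limits. Followed as written, section {20c} attenuates a real effect to (1 − m) × 0.25 when missingness is unrelated to active participation: 0.20 at 20% missing and 0.175 at 30%. When missingness differs by arm and both arms change over time, it biases the estimate in either direction and can raise the type I error to about 8%, or 11% with baseline adjustment, in the example worked here. The missingness rates, shared change and correlation behind these figures are all assumptions. The 80% power is not shown to fail: that depends on who is missing and on whether the model adjusts for baseline, and part of any shortfall comes from the 324 containing no loss allowance, whatever the method. The rule should still be changed before analysis, because it determines the primary estimate.

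**What to change.** - Replace the rule in section {20c} with a primary analysis valid under missing at random that includes every randomised participant and adjusts for baseline SCL-10. Either a mixed model on the SCL-10 measurements already scheduled in Table 1 or multiple imputation by arm would serve. With imputation, attendance in the exercise arm is a useful predictor; the per-protocol definition in section {20b} already requires it to be known.
- Keep baseline substitution as a sensitivity analysis, beside a delta-adjusted analysis that lets unobserved outcomes be worse than predicted.
- Align sections {20a} and {20c}, and stop describing the substitution as intention-to-treat.
- State in section {14} that the 80% power assumes complete primary outcomes, or that missing outcomes are confined to the inactive 37.5% if that was intended.

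The cost is wording and modest analysis work, with no new data. Section {20a} places the detailed analysis plan before data export, so the change can be made there. The downside is small: the primary result will rest on missing at random, which the sensitivity analyses probe.
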